### Dropout criteria

Participants will be dropped from the trial under the following conditions: (1) < 75% compliance with the protocol procedures (participating in < 6 of the 8 scheduled treatment sessions); (2) occurrence of a serious adverse event (SAE); (3) reluctance to continue the trial; (4) incomplete data that could influence the trial; (5) large errors in protocol or significant deviations in implementation; or (6) if the principal investigator (PI) or institutional review board (IRB) decides to terminate their participation in the trial.

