### Outcome measurements

In accordance with the study objective, improvements in pain intensity assessed using the VAS will be considered the primary outcome, and the secondary outcomes will be the changes in ODI and EQ-5D-5L. VAS, ODI, and EQ-5D-5L scores will be recorded before intervention, at the end of intervention, and 4 weeks after the completion of the intervention. The primary end point will be the VAS score recorded at the end of the intervention.

The VAS is a 10-cm-long straight line marked at each end with the anchor labels “no pain” and “pain as bad as it could be” [28]. Participants will be asked to mark a point representing the severity of their pain. Scores are recorded in millimeters, and the total score ranges from 0 to 100 mm [29].

The ODI has become one of the principal condition-specific outcome measures used in the management of spinal disorders [30]. The validated Korean version of the ODI, which excludes sexual life items from the original ODI, contains 9 questions about daily activities, including inventories of pain intensity, personal care, lifting, walking, sitting, standing, sleeping, social life, and traveling. Each question is rated on a scale from 0 to 5 points, with higher scores indicating greater severe pain-related disability [31].

The validated Korean version of the EQ-5D includes generic questions about personal health-related quality of life and 5 dimensions pertaining to mobility, self-care, usual activities, pain/discomfort, and anxiety/depression. Each dimension has 3 response categories, namely “none,” “some,” and “extreme/unable to,” with lower scores indicating a better state of health [32, 33]. The EQ-5D-5L is a new version of the EQ-5D that includes 5 levels of severity (none, slight, moderate, severe, and extreme/unable) for each of the 5 EQ-5D dimensions [34].

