### Sample size estimation

We had no preliminary study or adequate previous studies upon which to base sample size estimates. Therefore, we adopted a pilot study design. The appropriate sample size for two- or three-arm pilot studies is > 12 [35, 36]. Considering a dropout rate of 20%, we assigned 15 participants to each group (45 in total).

As our study is a pilot study, the sample size will not be sufficient for determining the efficacy of ILA for CLBP. Our study provides preliminary evidence for the efficacy and safety of ILA for CLBP.

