### Statistical analysis

A statistician not involved in data collection will analyze the final data. We will perform a full analysis set (FA group) to assess the efficacy and a supplementary per-protocol analysis (PP group). We will compare the results of the statistical analyses between the FA and PP groups and confirm any statistically significant differences between the groups. If a significant difference exists between the PP and FA groups, the cause will be reviewed and reflected in the efficacy assessment. Missing values will be obtained using the “last observation carried forward” method. Interim analyses will not be performed. All statistical analyses will be performed using the SPSS version 21 software.

Baseline characteristics will be described and compared between the groups. Continuous data will be presented as means and standard deviations and compared using the independent *t* test or Mann-Whitney *U* test (nonparametric test). Categorical data will be presented as frequencies and percentages and compared using the chi-square or Fisher exact test.

Within each group, changes in VAS, ODI, and EQ-5D-5L scores at 4 weeks (the end of intervention) and 8 weeks (4 weeks after the end of intervention) after the start of intervention, relative to the baseline score, will be analyzed using a paired *t* test or Wilcoxon signed rank test (nonparametric test). Trends over time and time-by-treatment interactions will be explored using repeated-measure analysis of variance. The degrees of changes in the VAS, ODI, and EQ-5D-5L scores at each time point between the groups will be evaluated using the independent *t* test or Mann-Whitney *U* test (nonparametric test). Subanalyses will be performed according to participant age. All reported *p* values will be two-sided, with 95% confidence intervals. A *p* value < 0.05 will be considered statistically significant.

A safety assessment will be performed for all AEs that will occur during the study period. The incidence of AEs and SAEs will be summarized by group and analyzed using the chi-square or Fisher exact test.

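### LOCF can fill a missing week-4 VAS only with the baseline value, so early losses kept in the full analysis set score a primary change of exactly zero

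*Protocol article*

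**What the plan says.** Under Outcome measurements the assessment schedule is: "VAS, ODI, and EQ-5D-5L scores will be recorded before intervention, at the end of intervention, and 4 weeks after the completion of the intervention". The same section fixes the primary time point: "The primary end point will be the VAS score recorded at the end of the intervention". That visit, at week 4, is the first one after baseline.

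Under Statistical analysis, the between-arm comparison is made on changes: "scores at each time point between the groups will be evaluated using the independent" t test or a Mann-Whitney test. The populations are given as: "We will perform a full analysis set (FA group) to assess the efficacy and a supplementary per-protocol analysis (PP group"). Who belongs to the FA set is not stated in the article. Missing data are covered by a single sentence: "Missing values will be obtained using the “last observation carried forward” method". No other method is named.

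Sample size estimation allows for losses: "Considering a dropout rate of 20%, we assigned 15 participants to each group (45 in total"). Dropout criteria remove participants for several reasons, some of which act during treatment, such as "participating in < 6 of the 8 scheduled treatment sessions".

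**The concern.** With no VAS between baseline and week 4, LOCF has only one value to carry to the primary end point: baseline. The imputed change is therefore zero by construction, and it enters the test as if it had been observed. Zero is a poor guess for the average participant in any arm. All arms, control included, receive real needling and real electroacupuncture, and entry requires a screening VAS of at least 40, so some fall through regression to the mean is likely everywhere.

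At week 8, the visit that shows whether an effect lasts, LOCF does two different things. A participant lost between weeks 4 and 8 has the week-4 score repeated, which assumes no later change. A participant lost before week 4 and kept in the set has baseline carried through, which assumes no effect at all.

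At stake are the size and the variance of the effect estimate. The article presents its results as a foundation for further research and plans two-sided tests at the 5% level, so distorted figures would pass into the next trial's design.

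**Working it through.** **The plan's own figure.** Sample size estimation starts from a pilot size of about 12 per arm and a 20% dropout allowance: 12 / (1 − 0.20) = 15 per arm, and 15 × 3 = 45. This reproduces. The allowance corresponds to 0.20 × 15 = 3 participants per arm.

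**Inputs from the article.** Three VAS assessments; week 4 primary; change scores compared between arms; LOCF; 15 per arm; two-sided 5% level.

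**Assumed inputs (the article gives none).** SD of change 20 mm; mean VAS falls of 20 to 40 mm; dropout unrelated to outcome; participants lost before week 4 stay in the FA set.

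**Formula.** Let m be the true mean fall in an arm and d the share lost before week 4. Those lost contribute 0, so the expected difference under LOCF is

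(1 − dT) × mT − (1 − dC) × mC,

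and the bias against the true difference mT − mC is dC × mC − dT × mT. If both arms have the same mean fall m, this reduces to (dC − dT) × m.

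**Equal loss, true difference.** With d = 0.20 in both arms, mC = 20 and mT = 40: 0.8 × 40 − 0.8 × 20 = 16 mm instead of 20 mm. By simulation of the t test, power is about 47% under LOCF, against about 65% when only the 12 observed values per arm are used. With falls of 20 and 30 mm, the difference goes from 10 to 8 mm.

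**Unequal loss, no true difference.** With 3 of 15 lost in one arm, none in the other and a 20 mm fall in both: (3/15) × 20 = 4 mm. Simulated type I error is about 7.6%, against about 5% on observed values.

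**Unequal loss, true difference.** With falls of 20 mm (control) and 30 mm (ILA), a true 10 mm becomes 0.8 × 30 − 20 = 4 mm if 20% are lost from ILA only, and 30 − 0.8 × 20 = 14 mm if 20% are lost from control only. The direction is not fixed.

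**Equal random dropout, no true difference.** With each participant in both arms having a 20% chance of loss, simulated bias is 0.0 mm and type I error 5.0%. With exactly 3 lost in each arm, type I error is about 3%.

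**How likely are the unequal splits?** With a 20% loss probability in each arm, a 3-versus-0 split in either direction has probability 2 × 0.250 × 0.035 = 1.8%. A gap of 3 or more of any kind has probability about 25%. If only 10% are lost before week 4, that falls to about 12%.

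**Week 8.** For a loss between weeks 4 and 8, the error equals the unseen change after week 4. It favours persistence only if pain returns. For a loss before week 4, the imputed week-8 change is 0, which works against persistence wherever pain has fallen. The net direction depends on the mix.

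**The case against.** The strongest reply is that the FA set is undefined. A reader might infer that every dropout before week 4 is scored as zero, but the article does not establish this. One of its dropout criteria is incomplete data, and the full protocol may require a post-baseline value for the FA set. LOCF would then do nothing at week 4. That point stands, and it makes the week-4 conclusion conditional. It does not remove the week-8 problem for participants lost after week 4.

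A reader might also infer that 20% dropout makes false positives common. It does not. When dropout is random at the same rate in all arms and the arms do not differ, the average bias is zero and type I error stays near 5%. The 25% figure is the chance of an imbalance, not a measure of bias. Nothing in the article suggests systematically different dropout: participants are blinded, and needling, schedule and electroacupuncture are the same across arms. Nor is the 20% a rate of loss before week 4. It is an overall allowance, and early loss may be smaller.

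It would likewise go too far to say that week 8 is biased towards persistence; early losses pull the other way. For a participant who left after few sessions, no change is a possible outcome, so zero is not absurd in each individual case.

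The article also says that the sample is too small to determine efficacy, and it adds a per-protocol analysis with a review of discrepancies. The first lowers the consequence. The second is only a partial check, because a per-protocol set is normally chosen on compliance and so does not repair the FA estimate.

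**Conclusion.** The point holds in conditional form. For anyone kept in the FA set without a week-4 VAS, LOCF fixes the primary change at exactly 0. For anyone lost between weeks 4 and 8, it repeats the week-4 score. At 20% loss before week 4 in both arms, a true difference is reduced by one fifth. If loss is unequal and the mean fall is the same in both arms, the contrast moves by the difference in loss shares times that fall: 4 mm for 3 versus 0 of 15 with a 20 mm fall. No direction can be stated in advance, at week 4 or at week 8.

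The millimetre and power figures rest on the assumed mean falls, the 20 mm SD and dropout unrelated to outcome. They scale with the loss that actually occurs before week 4. This is a should-fix rather than a must-fix, since no confirmatory efficacy decision rests on the pilot.

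**What to change.** Make the primary between-arm comparison a likelihood-based repeated-measures model on all observed VAS values, with arm-by-visit terms, baseline handled within the model and the week-4 contrast as primary. Use the same model for ODI and EQ-5D-5L. Keep LOCF, if at all, as a labelled sensitivity analysis. Report dropout by arm, with timing and reasons, so that a reader can judge how much the imputation matters.

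The cost is modest. No new data are needed, only rewording of the analysis section and a little programming, which the planned software can handle. The model assumes data missing at random, which is itself untestable. Under Quality assurance, protocol revisions need approval from the ministry and the IRB, and Trial status says that recruitment has ended. The change therefore has to be approved before the final data are analysed.

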### Inclusion criteria

Participants who meet all of the following criteria will be included in this trial: (1) aged between 19 and 70 years, (2) has CLBP lasting for at least the previous 3 months, (3) scored ≥ 40 points on a 100-mm VAS for pain at the time of screening, (4) has adequate level of Korean language proficiency for the reliable completion of all study assessments, and (5) voluntarily provides informed consent.

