## Discussion

Although LA has long been used in the treatment of CLBP, the efficacy and optimal treatment method of LLLT (including LA) for CLBP remains controversial owing to insufficient evidence. We designed this study to investigate the efficacy of ILA and the effects of different wavelengths of ILA on CLBP. The design of this study, including the treatment method, schedules, and outcome measurements, is based on the design of several studies that evaluated various types of acupuncture treatment for LBP [10, 13, 14, 19, 24, 25, 27]. The two modalities of ILA (650 and 830 nm) are based on our previous studies that showed that ILA has significant effects on neuropathic pain [37] and osteoarthritis [38] in rat models and previous RCTs that investigated the efficacy of LLLT on CLBP [13, 14].

Changes in VAS pain score will be recorded as the primary outcome, while changes in ODI and EQ-5D-5L scores will be recorded as secondary outcomes. This study will evaluate the effects of different wavelengths of ILA on pain reduction, pain-related functional disability, and quality of life in patients with CLBP.

This protocol has some limitations. First, owing to the lack of adequate preliminary studies and limited funding, this survey was designed as a single-center pilot study with a small sample size. Second, while previous LA studies on CLBP used noninvasive LA [13, 14, 19], we will only use ILA. Third, the factors that affect the effects of LA are wavelength, energy dose, and selected acupoints; however, we will only investigate the effects of wavelength. Fourth, although participants will be blinded to the group allocation and all outcome measures will be measured and recorded by an independent researcher to minimize the risk of detection bias, the acupuncturists cannot be blinded to the group allocation owing to the nature of LA.

Nevertheless, the results of this study are expected to provide preliminary evidence regarding the usefulness, safety, and efficacy of ILA for the treatment of CLBP and the effects of different wavelengths of ILA, and thus will provide a foundation for further research.

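### The between-group comparison uses unadjusted change scores although baseline is recorded for everyone; adjusting for baseline would give a modest, nearly free gain in precision

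*Protocol article*

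**What the plan says.** All references are to the protocol article.

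- **Between-group test (Statistical analysis).** A t test, with Mann-Whitney as the nonparametric alternative: "The degrees of changes in the VAS, ODI, and EQ-5D-5L scores at each time point between the groups will be evaluated using the independent". This is the only between-group test stated for the level of the scores, and it has no covariate.
- **Other longitudinal model (same section).** "Trends over time and time-by-treatment interactions will be explored using repeated-measure analysis of variance". It is exploratory, and no baseline covariate is given.
- **Data available (Outcome measurements).** "VAS, ODI, and EQ-5D-5L scores will be recorded before intervention, at the end of intervention, and 4 weeks after the completion of the intervention".
- **Primary variable.** Outcome measurements first says "improvements in pain intensity assessed using the VAS will be considered the primary outcome" and closes the same paragraph with "The primary end point will be the VAS score recorded at the end of the intervention". The Discussion says "Changes in VAS pain score will be recorded as the primary outcome".
- **Entry threshold (Inclusion criteria).** "scored ≥ 40 points on a 100-mm VAS for pain at the time of screening".
- **Size (Sample size estimation).** 15 per arm, 45 in total, from a pilot rule of thumb of 12 and 20% dropout. No SD, effect size or power is stated, and the section concedes that the sample cannot determine efficacy.

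**The concern.** A comparison of change scores treats each millimetre of baseline VAS as if it carried over in full to week 4. The carry-over is normally partial, so the subtraction does two unwanted things. It adds variance that a baseline-adjusted model would remove. It also over-corrects when the arms differ at baseline by chance: the arm that starts higher appears to improve more even if treatment does nothing. Both effects weigh most in small arms.

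The trial's stated product is preliminary evidence for later research, so the width of the confidence intervals is what is at stake. The covariate needed to narrow them is already collected. In addition, an unadjusted week-4 score and an unadjusted change give different contrasts when baselines differ, so the wording of the primary end point should leave no doubt about which is meant.

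**Working it through.** **Plan's own figure.** 12/(1 − 0.20) = 15 per arm, which reproduces. With 20% dropout, 15 × 0.80 = 12 complete per arm.

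**Inputs.** n = 15 per arm is from the article. The correlation ρ between baseline and week-4 VAS and the SDs are not given. I assume ρ = 0.3, 0.5, 0.7 and, where millimetres are needed, SD 20 mm.

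**Formula.** Write week-4 score = a + b × baseline + error. Then change = a + (b − 1) × baseline + error, so

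- Var(change) = Var(error) + (1 − b)² × Var(baseline)
- Var(adjusted) = Var(error) × [1 + 1/(2n − 4)]. The bracket is the average penalty for estimating b in a two-arm comparison: 1 + 1/26 = 1.038 at n = 15.

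**Case A: equal SDs, no truncation.** Here b = ρ, Var(change) = 2σ²(1 − ρ) and Var(error) = σ²(1 − ρ²). The large-sample ratio is (1 + ρ)/2.

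| ρ | (1 + ρ)/2 | × 1.038 | 15 per arm is worth | 95% CI half-width, change → adjusted (SD 20 mm) |
|---|---|---|---|---|
| 0.3 | 0.65 | 0.68 | 15/0.675 = 22 | 17.7 → 14.6 mm |
| 0.5 | 0.75 | 0.78 | 15/0.779 = 19 | 15.0 → 13.2 mm |
| 0.7 | 0.85 | 0.88 | 15/0.883 = 17 | 11.6 → 10.9 mm |

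A simulation of 20,000 trials gave ratios of 0.68, 0.78 and 0.88. With 12 per arm the penalty is 1 + 1/20 = 1.05, and the ratios are 0.68, 0.79 and 0.89.

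**Case B: the VAS threshold truncates baseline.** Assume mean 50 and SD 20 before selection, with baseline kept to 40–100. Selecting on baseline leaves the slope b and Var(error) = 400(1 − ρ²) unchanged, but it shrinks the baseline SD to 13.3 mm (variance 176.9). ρ below is the value before selection.

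| ρ | Var(error) | (1 − ρ)² × 176.9 | Ratio | × 1.038 | 15 per arm is worth |
|---|---|---|---|---|---|
| 0.3 | 364 | 86.7 | 364/450.7 = 0.808 | 0.84 | 17.9 |
| 0.5 | 300 | 44.2 | 300/344.2 = 0.872 | 0.91 | 16.6 |
| 0.7 | 204 | 15.9 | 204/219.9 = 0.928 | 0.96 | 15.6 |

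At ρ = 0.8 the same steps give 144/(144 + 7.1) × 1.038 = 0.99, so almost nothing is gained there. The threshold therefore reduces the benefit of adjustment. At ρ = 0.6, before the small-sample penalty, the ratio is 0.80 without the cut and 256/(256 + 0.16 × 176.9) = 0.90 with it.

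**Chance imbalance.** The SE of a baseline difference between two arms is SD × √(2/15): 13.3 × 0.365 = 4.9 mm, or 20 × 0.365 = 7.3 mm without truncation. A 5 mm imbalance is therefore ordinary. It displaces the change-score contrast by (1 − b) × 5 mm: 3.5, 2.5 and 1.5 mm at b = 0.3, 0.5 and 0.7.

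**Wording of the primary variable.** In the linear model, replacing week-4 score by change only lowers the baseline coefficient by 1. The arm effect and its CI are identical, so adjustment makes the choice between the two descriptions immaterial.

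**The case against.** The strongest reply is that nothing here is invalid. Under randomisation the change-score t test is unbiased, the trial is a declared pilot without a power claim, and no stated figure fails. That stands. The loss is one of efficiency, together with sensitivity to imbalance in the sample actually drawn. The pilot label does not remove the point, because a pilot's output is its estimates and their intervals.

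The repeated-measures analysis is not a remedy. It is exploratory, states no baseline covariate, and its time-by-treatment term also works on changes.

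A reader might infer four stronger points that the article does not support:

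- **That the entry threshold makes change scores even less efficient relative to adjustment.** It lowers the correlation, but it leaves the slope unchanged and shrinks baseline variance, so the gain falls. The threshold applies at screening. If baseline VAS is a separate measurement (assumed correlation with screening 0.8–0.9), the large-sample ratio at ρ = 0.6 is about 0.81–0.85, between the uncut 0.80 and the fully truncated 0.90.
- **That the SD handed to the next trial would be more precise.** The relative precision of an SD depends on degrees of freedom, and adjustment uses one more.
- **That the primary end point is contradictory.** The sentence naming the score at the end of intervention follows the list of visits and can be read as fixing the primary visit. Change in VAS at the end of intervention reconciles every statement, so the fault is loose wording.
- **That leaving t test or Mann-Whitney open is a defect.** A condensed article may leave that rule to the full protocol or SAP.

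**Conclusion.** The point holds as a recommendation on efficiency and clarity. The article fixes an unadjusted change-score comparison while recording the baseline values that would improve it. At 15 per arm, adjustment cuts the variance of each pairwise comparison by about 32%, 22% and 12% at ρ = 0.3, 0.5 and 0.7 if SDs are equal. If the entry threshold truncates baseline as assumed, the cut is about 16%, 9% and 4%. The equal-SD figures are best read as the upper end. The gain nearly vanishes at ρ = 0.8 under truncation. All of these sizes rest on assumed correlations and SDs. The existence of a gain over the range 0.3 to 0.7 does not depend on which of the two cases applies.

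The finding does not show that the planned test is biased or that the trial's conclusions would be wrong.

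**What to change.** 1. State one primary variable: VAS at the end of intervention (week 4).
2. Analyse it in a linear model with arm as factor and baseline VAS as covariate, and report the adjusted pairwise mean differences with 95% CIs.
3. Use the same form for ODI and EQ-5D-5L, each with its own baseline score.
4. Align Outcome measurements, Statistical analysis and Discussion on that single definition.

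The cost is wording and one degree of freedom; no new data are needed. The Trial status section says that recruitment has closed and that procedures were due to finish by the end of December 2020. The change should therefore be recorded before anyone sees results by arm. If that is no longer possible, the adjusted analysis should be reported beside the planned one and labelled as added later.
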